## 7.6. DOSING DELAYS/DOSE MODIFICATIONS AND ADVERSE EVENT MANAGEMENT

### 7.6.1. Immune related adverse events (irAE)

IrAR may be defined as an adverse event of unknown etiology, associated with drug exposure and is consistent with an immune phenomenon.

irAEs may be predicted based on the nature of the Avelumab compound, its mechanism of action, and reported experience with immunotherapies that have a similar mechanism of action. Special attention should be paid to AEs that may be suggestive of potential irAEs. An irAE can occur shortly after the first dose or several months after the last dose of treatment.

If an irAE is suspected, efforts should be made to rule out neoplastic, infectious, metabolic, toxin or other etiologic causes prior to labeling an adverse event as an irAE.

Restart Avelumab if the adverse reaction remains at Grade 1 or less. If another episode of a severe adverse reaction occurs, permanently discontinue Avelumab.

Patient requiring 2 or more consecutive cancellations of Avelumab injection should permanently discontinue avelumab. Note that further treatment by regorafenib monotherapy will be allowed until disease progression, unacceptable toxicity, etc. (see section 3.2.2 for more details).

For management, refer to the appendix 8 and to most updated Investigator Brochure.

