#### **11.2.6. Intensity criterion**

It is important to distinguish between serious and severe AEs. Severity is a measure of intensity whereas seriousness is defined by the criteria in Section 11.2.2. An AE of severe intensity need not necessarily be considered serious. For example, nausea that persists for several hours may be considered severe nausea, but not a SAE. On the other hand, a stroke that results in only a limited degree of disability may be considered a mild stroke but would be a SAE.

The CTEP Active Version of the NCI Common Terminology Criteria for Adverse Event (CTCAE) will be utilized for AE reporting.

The intensity of adverse events not listed in this classification will be assessed using the following descriptors:

Mild (grade 1): does not affect the patient's usual daily activities,  
Moderate (grade 2): disturbs the patient's usual daily activities,  
Severe (grade 3): prevents the patient's usual daily activities,  
Very severe (grade 4): requires critical care/life-threatening,  
Death (grade 5).

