| Grade 1 or Grade 2 endocrinopathies (hypothyroidism, hyperthyroidism, adrenal insufficiency, type I diabetes mellitus) | No change                                                                                                                                                                | 
Continue Avelumab therapy
Endocrinology consult if needed
 
Start thyroid hormone replacement therapy (for hypothyroidism), anti-thyroid treatment (for hyperthyroidism), corticosteroids (for adrenal insufficiency) or insulin (for Type I diabetes mellitus) as appropriate.
 
Rule-out secondary endocrinopathies (i.e. hypopituitarism / hypophysitis)
                                                                                        | Continue hormone replacement/suppression and monitoring of endocrine function as appropriate.                                                                                                                                                                                                                                                               |
| Grade 3 or Grade 4 endocrinopathies (hypothyroidism, hyperthyroidism, adrenal insufficiency, type I diabetes mellitus) | 
Delay until <math>\leq</math> grade 2 and reduce 1 dose level
 
For grade 4, permanent discontinuation can be considered at treating investigator discretion
 | 
Withhold Avelumab therapy
Consider hospitalization
Endocrinology consult
 
Start thyroid hormone replacement therapy (for hypothyroidism), anti-thyroid treatment (for hyperthyroidism), corticosteroids (for adrenal insufficiency) or insulin (for type I diabetes mellitus) as appropriate.
 
Rule-out secondary endocrinopathies (i.e. hypopituitarism / hypophysitis)
                                                                     | 
Resume Avelumab once symptoms and/or laboratory tests improve to Grade <math>\leq</math> 1 (with or without hormone replacement/suppression).
 
Continue hormone replacement/suppression and monitoring of endocrine function as appropriate.
                                                                                                   |

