|-----------------------------------------------------------------|------------------------------------------------------------------------------------|------------------------------------------------------------------------------------------------------------------------------------------------------------------------------------------------------------------------------------|------------------------------------------------------------------------------------------------------------------------------------------------------------|
|                                                                 |                                                                                    | Initial Management                                                                                                                                                                                                                 | Follow-up Management                                                                                                                                       |
| Grade 1
Creatinine increased > ULN to 1.5 x ULN       | No change                                                                          | Continue Avelumab therapy                                                                                                                                                                                                          | Continue renal function monitoring
If worsens:
Treat as Grade 2 to 3 or 4.                                                                           |
| Grade 2 to 3
Creatinine increased > 1.5 and ≤ 6 x ULN | No change for grade 2
Delay until ≤ grade 2 and reduce 1 dose level for grade 3 | Withhold Avelumab therapy
Increase frequency of monitoring to every 3 days
1.0 to 2.0 mg/kg/day prednisone or equivalent.
Add prophylactic antibiotics for opportunistic infections
Consider renal biopsy              | If returns to Grade ≤1:
Taper steroids over at least 1 month, and resume Avelumab therapy following steroids taper.
If worsens:
Treat as Grade 4. |

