| Grade 2 irAE or first occurrence of Grade 3 irAE                                                                                                                                                                              | No change for grade 2

Delay until $\leq$ grade 2 and reduce 1 dose level for grade 3 | Withhold Avelumab therapy 1.0 to 2.0 mg/kg/day prednisone or equivalent
Add prophylactic antibiotics for opportunistic infections
Specialty consult as appropriate                                           | If improves to Grade $\leq$ 1: Taper steroids over at least 1 month and resume Avelumab therapy following steroids taper.                                             |
| Recurrence of same Grade 3 irAEs                                                                                                                                                                                              | Permanently discontinue                                                                     | Permanently discontinue Avelumab therapy 1.0 to 2.0 mg/kg/day prednisone or equivalent
Add prophylactic antibiotics for opportunistic infections
Specialty consult as appropriate                            | If improves to Grade $\leq$ 1: Taper steroids over at least 1 month.                                                                                                  |
| Grade 4                                                                                                                                                                                                                       | Permanently discontinue                                                                     | Permanently discontinue Avelumab therapy 1.0 to 2.0 mg/kg/day prednisone or equivalent and/or other immunosuppressant as needed
Add prophylactic antibiotics for opportunistic infections
Specialty consult. | If improves to Grade $\leq$ 1: Taper steroids over at least 1 month                                                                                                   |

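### Section 7.6.1 and Appendix 8 give opposite instructions on re-starting avelumab after a repeated Grade 3-4 endocrinopathy (and, read broadly, after a second severe immune event of a different type), and no text says which prevails

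*Protocol*

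**What the plan says.** Section 7.6.1 of the protocol, on immune-related adverse events, gives three rules for avelumab and a cross-reference:

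- Restart: "Restart Avelumab if the adverse reaction remains at Grade 1 or less".
- Second severe event: "If another episode of a severe adverse reaction occurs, permanently discontinue Avelumab".
- Missed doses: a patient who needs two or more injections in a row cancelled stops avelumab for good and may go on with regorafenib alone.
- Cross-reference: "For management, refer to the appendix 8 and to most updated Investigator Brochure".

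The relevant avelumab rules in Appendix 8 are these:

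- Endocrine disorders, Grade 3 or 4: withhold, then "Resume Avelumab once symptoms and/or laboratory tests improve to Grade" 1 or lower, whether or not the patient is on replacement hormones. The avelumab columns of this row contain no permanent stop and no recurrence rule, and require no general steroid taper.
- Creatinine, Grade 2 to 3: withhold, give steroids and, on return to Grade 1 or lower, "Taper steroids over at least 1 month, and resume Avelumab therapy following steroids taper". There is no recurrence rule; the permanent stop is at Grade 4.
- Other immune-related events: the row headed "Grade 2 irAE or first occurrence of Grade 3 irAE" withholds and resumes after a taper. The row headed "Recurrence of same Grade 3 irAEs" stops permanently.

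**The concern.** The two places govern the same decision: whether a patient who has had a second severe immune event receives avelumab again. If they disagree and neither is given precedence, sites can treat the same situation in opposite ways while each follows the protocol. The trial runs 17 phase II cohorts in 7 centres under this one text.

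The stake is first patient safety. There is also a smaller statistical one. Section 7.6.1 lets a patient who has stopped avelumab continue on regorafenib alone, so the choice of page decides whether later exposure is to the combination or to one drug.

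**Working it through.** There is no figure to reproduce. The check sets the two texts side by side, case by case.

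Two points of reading come first. Section 7.6.1 does not define severe. Section 11.2.6 equates severe with grade 3 in the scale it gives for events not listed in CTCAE, so Grade 3 or above is assumed here. The phrase about another episode can be read narrowly (the same reaction returns) or broadly (any second severe reaction).

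| Case | 7.6.1, narrow | 7.6.1, broad | Appendix 8 | Conflict? |
|---|---|---|---|---|
| Grade 3-4 endocrinopathy recurs | stop | stop | withhold, resume | yes, on both readings |
| Grade 3 creatinine increase recurs | stop | stop | withhold, taper, resume | yes, on both readings |
| A Grade 3 event, then a first Grade 3 event of another type in the other-events table | no stop | stop | withhold, taper, resume | on the broad reading only |
| The same Grade 3 colitis, rash or other event recurs | stop | stop | stop | no |
| First Grade 3-4 pneumonitis, or immune-related myocarditis | second-episode rule not reached | second-episode rule not reached | stop at once | not on this point |

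**Can silence in the endocrine and creatinine rows mean an implied stop?** That is hard to sustain. Appendix 8 writes a recurrence stop where it wants one: for colitis, rash, hepatic events and other immune-related events. In the endocrine row, the regorafenib column does mention permanent discontinuation at Grade 4; the avelumab columns do not.

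**How does the two-cancellation rule interact?** Avelumab is due every 14 days (Section 7.3). A taper of at least one month lasts at least 28 days, and 28 / 14 = 2 scheduled injections fall inside it, before counting the time needed to reach Grade 1. If a withheld injection counts as cancelled, the rule is met during the taper.

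- Creatinine increase, Grade 3 colitis, Grade 3 rash and other Grade 2-3 events all resume only after such a taper. A patient following Section 7.6.1 would usually be off avelumab after the first event, so a second event on avelumab would seldom arise.
- The Grade 3-4 endocrine row has no such taper. An event that settles with at most one missed injection leaves the patient on avelumab, and a recurrence then meets the conflict directly.
- The same arithmetic exposes a further mismatch: Section 7.6.1 ends avelumab at two consecutive cancellations, while several Appendix 8 rows instruct resumption after a taper that would normally use up at least two.

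**Is there a tie-break?** Section 7.6.2 says that when several events carry conflicting recommendations, the one giving the lowest dose level applies. That ranks recommendations for different events, not two texts on one event, and avelumab is 10 mg/kg at every level in its table. Section 7.6.2 also refers severe toxicity to the principal investigator, without saying which text that person should apply.

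**The case against.** The strongest reply has four parts.

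First, the sentence on another episode follows a sentence about the adverse reaction, so the narrow reading is natural. On that reading Section 7.6.1 agrees with the colitis, rash and other-events rows. This stands: for two events of different types the text is ambiguous, not plainly contradictory. It does not help the endocrine or creatinine rows.

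Second, a reader might infer that Appendix 8 stops avelumab only when the same Grade 3 event recurs. It does not support that. It also stops avelumab for Grade 3-4 pneumonitis, immune-related myocarditis, Grade 4 colitis, rash, creatinine increase and other immune-related events, recurrent hepatic events, Grade 2 or 3 events lasting 12 weeks or more, and steroid need of 10 mg per day or more for over 12 weeks.

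Third, the two-cancellation rule removes many apparent conflicts. A patient with Grade 3 colitis and later Grade 3 rash is a tempting example, but the taper for the colitis would usually have ended avelumab already. The rule also means that an endocrinopathy with a long hold could end avelumab, so it would be wrong to say the protocol never stops it for these events. This too stands, provided a withheld dose counts as a cancellation, which the protocol does not state.

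Fourth, a general sentence that defers to event-specific tables, with severe cases referred to the principal investigator, could be taken as an implied hierarchy. That is plausible but not written, and Section 7.6.1 states its stop as a rule, not as a default.

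**Conclusion.** The point holds in a limited form. A repeated Grade 3-4 endocrinopathy gets opposite instructions from Section 7.6.1 and Appendix 8 on any reading of the former. A repeated Grade 3 creatinine increase does so on paper, although the two-cancellation rule would usually act first. A second severe event of a different type does so only on the broad reading. No text settles which page prevails.

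The number of patients affected cannot be estimated: the documents give no event frequencies. A reader might infer that every patient with two different Grade 3 or higher immune events is affected. The documents do not support this, because many such patients would already have stopped under another rule. Nor do they show any effect on response rates. Sample size, type I error and power are untouched.

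The conclusion rests on taking severe as Grade 3 or above and on the absence of a precedence rule in the protocol. The Investigator's Brochure, to which both sections also refer, was not available. This is a matter of document consistency with a safety consequence, and it is worth correcting.

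**What to change.** Reconcile Section 7.6.1 with the endocrine, creatinine and other-events rows of Appendix 8. The reconciled text should state:

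1. whether the second-episode stop is triggered by the same reaction or by any severe reaction, and what grade counts as severe;
2. whether it applies to endocrinopathies and creatinine increases;
3. whether a withheld injection counts as a cancellation, and how the two-cancellation rule applies to rows that resume after a steroid taper.

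Then use the same wording in both places, or state which text prevails. The choice of clinical rule belongs to the sponsor and investigators; none is proposed here. The cost is a wording change in the next amendment and a note to sites, with no change to design or analysis.

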### 7.6.2. Management of Adverse Events

Any toxicity observed during the course of the study could be managed by interruption and/ or dose reduction of the dose if deemed appropriate by the Investigator. Dose adjustments are to be made according to the greatest degree of toxicity (please refer to the IMP Investigator's Brochure), and in accordance with table below:

| Level       | -1        | 1          | 2          |
|-------------|-----------|------------|------------|
| Avelumab    | 10 mg/kg  | 10 mg/kg   | 10 mg/kg   |
| Regorafenib | 80 mg x 1 | 120 mg x 1 | 160 mg x 1 |

Adverse events will be graded using the NCI Common Terminology Criteria for Adverse Events Version (CTCAE) v5.0.

The following guidelines outline dose adjustments for the most frequent of these toxic effects. If any severe toxicity occurs it should be referred to the principal investigator in order to decide management in the best interest of the patient. If a patient experiences several adverse events with conflicting recommendations, please use the dose modification recommendation that reduces the dose to the lowest level.

Once a dose has been reduced, it will in no case be increased again.

For all cohorts except cohort [A'], patients requiring a delay of > 4 weeks OR > one dose reduction (of Regorafenib) if RP2D is 120mg of Regorafenib and > 2 dose reductions if RP2D is 160mg of Regorafenib should permanently discontinue regorafenib. Note that further treatment by avelumab monotherapy will be allowed until disease progression, unacceptable toxicity, etc. (see section 3.2.2 for more details).

For cohort [A'], regorafenib should be interrupted and no dose reduction are allowed. Patients requiring a delay of > 4 weeks should permanently discontinue regorafenib. Note that further treatment by avelumab monotherapy will be allowed until disease progression, unacceptable toxicity, etc. (see section 3.2.2 for more details).

Patient should go off study if regorafenib has been permanently discontinued before first dose of avelumab.

Please refer to Appendix 7 and 8 and to most updated Investigator Brochure for management of toxicities.

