### 3.2.2. Treatment scheme

Regorafenib will be taken orally once daily for three weeks on/one week off, as appropriate for assigned dose level.

Avelumab will be administered intravenously, at fixed doses of 10 mg/kg, every two weeks, starting on Cycle 1 Day 15.

A treatment cycle consists of 4 weeks. Treatment may continue until disease progression or study discontinuation (withdrawal of consent, intercurrent illness, unacceptable adverse event or any other changes unacceptable for further treatment, etc.).

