## **5.2. DEFINITIONS OF DURATION OF STUDY AND TREATMENT (PER PATIENT)**

Patients will receive study treatment as long as it is considered to be in their best interest. Patients will be evaluated at scheduled visits in up to five study periods:

- **Pre-treatment (PRE TT):** from signature of informed consent to the first administration of study drugs.
- **Treatment (TT):** from the first administration of study drugs to treatment discontinuation
- **Safety follow-up (SFUP):** after treatment discontinuation, safety follow-up must be performed 30 days after the last treatment administration (toxicity assessment).
- **Extended safety follow-up (ESFUP):** given the potential risk for delayed immune-related toxicities, extended safety follow-up must be performed up to 90 days after the last dose of avelumab administration (ie. 60 days after SFUP). This visit may be performed either via a site visit or via a telephone call with subsequent site visit requested in case any concerns noted during the telephone call
- **Follow-up (FUP):**

After safety follow-up visit, patients who discontinue treatment without progression will be followed **every 12 weeks until:**

1. Disease progression,
2. Initiation of other antitumor therapy,
3. Death, or
4. The date of study termination, whichever occurs first.

After documented progression or start of a new antitumor therapy, patients will be **followed every 6 months until:**

1. Death, or
2. The date of study termination, whichever occurs first.

Patients will be considered to be **on-study** from the signature of the informed consent to the end of follow-up period.

Patients will be considered to be **on-treatment** for the duration of their treatment until 90 days after the last treatment administration, except if the patient starts a new antitumor therapy before this period. Patients may withdraw their consent at any time; no further study activities will be conducted on them.

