## 5.6. EVALUATION AT SAFETY FOLLOW-UP VISIT

The safety follow-up will be scheduled 30 days (4 weeks) after the last treatment administration (a window of  $\pm 1$  week is allowed). In case of the patients starts a new antitumor therapy, this visit must be done before the date of administration of this new antitumor therapy.

Regardless of the reason for discontinuation, the complete workup has to be done at the end-of-treatment visit. This will include the following assessments:

- Assessment of signs and symptoms.
- Complete physical examination.
- ECOG performance status.
- Vital signs [heart rate, blood pressure, and temperature].
- Hematology.
- Biochemistry.
- Thyroid function.
- Urinalysis.
- Calculated CrCl.
- Clinical and radiological tumor assessment (MRI) (except for patients with confirmed PD at discontinuation or who had started a new treatment).
- Intercurrent events and concomitant disease and treatments.
- Safety assessment (AEs).

Adverse events and SAE must be reported for 30 days after the last treatment administration or until the start of a new antitumor therapy, whichever occurs first. Note that even if the patient has started a new antitumor therapy, all AE and SAE suspected to be treatment-related will be reported until 30 days after the last treatment administration.

**Moreover, extended safety follow-up (ESFUP)** must be performed up to 90 days after the last dose of avelumab administration (ie. 60 days after SFUP). This visit may be performed either via a site visit or via a telephone call with subsequent site visit requested in case any concerns noted during the telephone call. Beyond this period of time, only those SAEs suspected to be treatment-related will be reported (see Section 11).

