#### Rules of decision for patient's replacement:

- Any patient not eligible or not assessable for efficacy will be replaced.
- However, any patient who received at least one administration of the study drug will be included in the safety analysis.

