#### 11.6. NON SERIOUS ADVERSE EVENT

| TYPE OF EVENT  | REPORTING PROCEDURES    | DEADLINE FOR REPORTING TO THE SPONSOR    |
|----------------|-------------------------|------------------------------------------|
| Non-serious AE | Case report/record form | Does not need to be reported immediately |

Non-serious adverse events will be reported by the investigator in the patient's CRF and will be followed up until complete resolution.

The following variables will be collected for each AE:

- AE (verbatim)
- The date when the AE started and stopped
- Minimum and maximum intensity
- Whether the AE is serious or not
- Outcome
- Investigator causality rating against the Investigational Product (yes or no) radiotherapy (yes/no)
- Action taken with regard to investigational product/comparator/combination agent
- Treatments given to treat AE

If an adverse event becomes serious, it should be reported and followed-up as mentioned in the previous reporting procedures.

If the investigator would like to decrease trial treatment dose or temporarily stop study management without respecting protocol procedures, he/she should have previously discussed with the coordinator. However, symptomatic treatment can be prescribed to manage the adverse event.

Any definitive interruption of the procedure has to be immediately notified to the sponsor. The patient remains in the study and is followed-up according to the procedures described in the protocol.

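### Section 7.6.2 takes a patient off study when regorafenib stops for good before avelumab starts, while sections 5.2, 5.6, 5.7 and 11.6 keep that patient in safety and survival follow-up

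*Protocol*

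**What the plan says.** Regorafenib starts on day 1. Avelumab is given "every two weeks, starting on Cycle 1 Day 15" (section 3.2.2), so days 1 to 14 are regorafenib alone. For a permanent stop in that window, section 7.6.2 states: "Patient should go off study if regorafenib has been permanently discontinued before first dose of avelumab".

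Other sections govern what happens after treatment stops:

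- Section 5.2 counts a patient as on study "from the signature of the informed consent to the end of follow-up period" and defines the on-treatment period separately. It adds: "After safety follow-up visit, patients who discontinue treatment without progression will be followed", at 12-week intervals, then every 6 months after progression or new therapy. The exemption it gives is "Patients may withdraw their consent at any time; no further study activities will be conducted on them".
- Section 5.6 schedules a visit 30 days after the last treatment and says: "Regardless of the reason for discontinuation, the complete workup has to be done at the end-of-treatment visit".
- Section 5.7 repeats the 12-week and 6-month schedules, the latter to death or study termination, and exempts only patients who withdraw consent.
- Section 11.6, on a definitive interruption, says: "The patient remains in the study and is followed-up according to the procedures described in the protocol".

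For the phase II analysis sets, section 10.2.2 says "any patient who received at least one administration of the study drug will be included in the safety analysis".

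**The concern.** The protocol defines study participation and treatment separately, so on its own terms leaving the study means that follow-up ends. Section 7.6.2 uses the study term for a group that the other sections keep under observation. It neither refers to those sections nor describes itself as an exception to them.

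Two sites could both follow the protocol and collect different data on the same kind of patient. Some of these patients will have stopped for early regorafenib toxicity: Appendix 8 requires permanent discontinuation for grade 4 hypertension, for transaminases above 20 times the upper limit of normal, and for grade 4 diarrhoea or rash. At stake is the completeness of scheduled safety and survival data for patients who stay in the safety denominator.

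**Working it through.** The protocol states no figure to reproduce. The check compares the texts and then traces such a patient through the analysis rules.

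1. **Meaning of off study.** Section 5.2 ends on-study status at the end of follow-up and gives on-treatment status its own end. Read with those definitions, section 7.6.2 ends follow-up, not only dosing.

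2. **Exceptions elsewhere.** Sections 5.2 and 5.7 exempt patients who withdraw consent. Neither they nor 5.6 or 11.6 exempt a stop before avelumab. The conflict is therefore direct.

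3. **Visits that depend on the reading.** If the last regorafenib dose is on day 14 at the latest, the 30-day work-up falls by day 14 + 30 = day 44. Ninety days after that dose is day 14 + 90 = day 104. Survival contacts follow every 6 months. Under 7.6.2 none of these is scheduled; under 5.2, 5.6 and 5.7 the 30-day work-up and the survival contacts are.

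4. **Extended safety follow-up.** Sections 5.2 and 5.6 time it from the last avelumab dose, which this patient never receives. Both add that this equals 60 days after the 30-day visit, but as an explanation of the avelumab timing, not as a separate rule. Removing the 7.6.2 wording would still leave this date open.

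5. **Safety population.** Section 10.2.2 includes anyone who started either drug, so the patient is counted. The interim safety analysis in 10.3.2.3 covers cycle 1 for the first ten phase II patients. A patient who leaves by day 14 contributes at most 14/28 = 50% of that window, and one patient is 1/10 = 10% of that analysis.

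6. **Phase II efficacy.** Section 10.2.2 requires one complete cycle of both drugs or two incomplete cycles within the first two, and normally a disease measurement at least eight weeks after treatment onset. With avelumab on schedule, a stop by day 14 gives one incomplete cycle. The patient is not assessable, is replaced, and is outside the population that 10.3.2.2 uses for the primary and other efficacy endpoints.

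7. **Phase I.** Such a patient has at most 14/21 = 67% of planned cycle 1 regorafenib and no avelumab. Both are at or below the 75% relative dose intensity limit, so section 10.2.1 already counts a toxicity stop as a dose-limiting toxicity without replacement. The DLT count does not depend on later follow-up.

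**The case against.** The best defence is context. The sentence stands in a dosing section, just after two paragraphs that allow avelumab alone once regorafenib has stopped. Its likely purpose is to rule that option out when no avelumab has yet been given, with the study term used loosely for treatment. A site reading 5.2, 5.6 and 5.7 would have a consistent follow-up schedule. Section 11.6 is also headed for non-serious events, so its sentence is not the natural place to look. This may well explain the intent, but it does not remove the conflict: 5.2 defines the study term, and 7.6.2 uses it without qualification.

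The defence is stronger on consequences, and three larger readings are tempting:

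- A reader might infer that survival is informatively censored near day 14, with each patient worth 1/50 = 2.0 to 1/43 = 2.3 percentage points of a cohort's 1-year OS. The protocol does not support this: with avelumab on schedule these patients are not in that denominator. Only a patient given regorafenib in both of the first two cycles while avelumab was delayed could qualify, and that stop would not be at day 14.
- A reader might infer that early severe toxicity goes unrecorded and that safety rates are understated. Section 5.6 has adverse events reported for 30 days after the last treatment, or until new therapy begins, with suspected related events still reported to day 30. Section 5.7 follows related events until they resolve or stabilise. Section 11.3 has SAEs reported to 90 days after the last dose or until new therapy, related SAEs without time limit, and allows medical follow-up beyond withdrawal. The event behind the stop should be captured.
- A reader might want a count of affected patients. The protocol gives no rate. The triggers in 7.6.2 itself, a delay beyond 4 weeks or repeated dose reductions, can hardly be met within 14 days, and some stops will be for refusal or progression.

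**Conclusion.** The inconsistency is real and should be corrected; its effect is limited. It decides whether scheduled safety visits and survival contacts take place for patients who stop regorafenib before avelumab but stay in the safety population. Non-serious events, and later events not suspected to be related, may be missed, and completeness may differ between sites. The protocol does not support a claim of biased phase II survival estimates or of lost serious toxicity.

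The number of patients cannot be stated without a stopping rate, which the protocol lacks. The largest proportion that can be shown is one patient in ten in the interim safety analysis, if such a patient falls among those ten. The conclusion on efficacy assumes that avelumab was due on schedule at Cycle 1 Day 15.

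**What to change.** Reconcile section 7.6.2 with 5.2, 5.6, 5.7 and 11.6. The treatment consequence is for the sponsor to settle. The text should state that patients whose regorafenib is permanently stopped before any avelumab continue in safety and survival follow-up, with a cross-reference to 5.2, 5.6 and 5.7. Sections 5.2 and 5.6 should also give the reference date for the extended safety follow-up when no avelumab was given.

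The cost is one or two sentences in an amendment and a few follow-up contacts. Sample sizes, endpoints and analysis populations do not change.
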